# The SNAP trial: a double blind multi-center randomized controlled trial of a silicon nitride versus a PEEK cage in transforaminal lumbar interbody fusion in patients with symptomatic degenerative lumbar disc disorders: study protocol

**DOI:** 10.1186/1471-2474-15-57

**Published:** 2014-02-25

**Keywords:** Disc degeneration, Spondylolisthesis, Lumbar interbody fusion, PEEK, Silicon nitride, Ceramic implant, Randomized controlled trial

## Abstract

**Background:**

Polyetheretherketone (PEEK) cages have been widely used in the treatment of lumbar degenerative disc disorders, and show good clinical results. Still, complications such as subsidence and migration of the cage are frequently seen. A lack of osteointegration and fibrous tissues surrounding PEEK cages are held responsible. Ceramic implants made of silicon nitride show better biocompatible and osteoconductive qualities, and therefore are expected to lower complication rates and allow for better fusion.

Purpose of this study is to show that fusion with the silicon nitride cage produces non-inferior results in outcome of the Roland Morris Disability Questionnaire at all follow-up time points as compared to the same procedure with PEEK cages.

**Methods/Design:**

This study is designed as a double blind multi-center randomized controlled trial with repeated measures analysis. 100 patients (18–75 years) presenting with symptomatic lumbar degenerative disorders unresponsive to at least 6 months of conservative treatment are included. Patients will be randomly assigned to a PEEK cage or a silicon nitride cage, and will undergo a transforaminal lumbar interbody fusion with pedicle screw fixation. Primary outcome measure is the functional improvement measured by the Roland Morris Disability Questionnaire. Secondary outcome parameters are the VAS leg, VAS back, SF-36, Likert scale, neurological outcome and radiographic assessment of fusion. After 1 year the fusion rate will be measured by radiograms and CT. Follow-up will be continued for 2 years. Patients and clinical observers who will perform the follow-up visits will be blinded for type of cage used during follow-up. Analyses of radiograms and CT will be performed independently by two experienced radiologists.

**Discussion:**

In this study a PEEK cage will be compared with a silicon nitride cage in the treatment of symptomatic degenerative lumbar disc disorders. To our knowledge, this is the first randomized controlled trial in which the silicon nitride cage is compared with the PEEK cage in patients with symptomatic degenerative lumbar disc disorders.

**Trial registration:**

NCT01557829

## Background

Chronic low back pain is an important reason for patients to visit general practitioners. In Europe, estimates of lifetime prevalence of chronic low back pain range from approximately 60–90% [1]. It is one of the leading causes of activity limitation in adults and results in high socio-economic costs and loss of quality of life [2]. The exact cause of chronic low back pain is often unknown, but degenerative disorders of the intervertebral disc are held responsible [3]. The pain can be eliminated by stabilizing the degenerative segment, for example as seen in the successful treatment of degenerative joints with an arthrodesis [4,5]. Spinal fusion is commonly used for stabilizing degenerative and isthmic spondylolisthesis and severe, painful disc degeneration.

In a spinal fusion, two or more vertebrae are fused after a bone bridge is created between the vertebrae, either posterior, interbody or both. Originally, bone grafts were used to promote interbody fusion. However, several complications were associated with the use of grafts. These include donor site morbidity, a decrease in the intervertebral disc space height due to graft collapse, graft subsidence, graft retropulsion, graft resorption, fusion failure with subsequent pseudarthrosis and prolonged healing time [6,7].

As an alternative for bone grafts, interbody cages were developed [7]. They are designed to be filled with bone, allowing bony fusion through the cage to the adjacent vertebrae. Both material and design of the cage play an important role in correcting spinal deformities and creating an optimal environment for spinal fusion [8-10]. The development of a solid bony fusion is influenced by mechanical and biological factors. For example, the size and geometry of the cage determines the initial mechanical stability [11,12]. Furthermore cage stiffness is an important factor in stress shielding [13,14]. Biological factors, such as the osteointegration of the surface of the cage, influence quality, speed and attachment of newly formed bone [8].

Cages allow for direct axial load bearing and restore of height of the intervertebral and foraminal space. Initially, interbody cages were implanted in pairs via the traditional posterior lumbar interbody fusion (PLIF) technique. More recently, a larger single oblique cage is used that provides more stability [15,16].

Polyetheretherketone (PEEK) materials were used in aerospace and aviation industries before researchers began exploring them in medical devices, mainly in trauma and femoral components of hip prosthesis [17,18]. Besides being radiolucent, PEEK is relatively inert and does not provoke a strong foreign body reaction in vivo [19]. During the late 1990’s the first PEEK cages for spinal fusion became available. High fusion rates and good to excellent clinical outcomes have been reported compared to titanium cages and bone grafts [20,21]. Most spine surgeons therefore prefer PEEK cages over other cages.

To allow some visualization on radiograms and CT, radio-opaque markers are present in PEEK cages. The major advantage of PEEK cages over the metal cages is that they produce less artifacts on CT or MR scans. However, a radiolucent cage could also contribute to the difficulty of radiographic assessment of its exact position in the spine. For example, placement of the cage during surgery is less accurate, and follow-up imaging is more difficult. This is important to determine the cause of ongoing symptoms and/or to determine if fusion has occurred. Additional problems observed include a 14.3% rate of subsidence in patients with PEEK cages after lumbar interbody fusion [22]. Furthermore, posterior migration of a component of a PEEK cage has been reported [23]. It has also been reported that PEEK cages are generally encapsulated by a thin fibrous tissue layer rather than bone growing in intimate contact with the polymer [24].

Better osteointegration of the cage is believed to minimize the rate of subsidence and migration. Therefore, researchers have been working on materials that mimic the mineral content of bone for many years [25]. Ceramic implants can be manufactured with a rough surface and have the potential to show a better integration with the host bone, which facilitates the attachment of bone to the implant rather than the fibrous encapsulation [24]. Ceramics are strong and light-weight and have desirable imaging properties, free from artifacts on CT and MRI [26].

Silicon nitride (Si_3_N_4_) is a ceramic with a compression strength exceeding the usual plastic and metal materials used for interbody cages. Unlike many other ceramics, silicon nitride resists brittle fractures; its toughness exceeds that of alumina, a material with 30+ years of use in joint replacements [27]. Silicon nitride is also highly compatible with standard imaging techniques. The material is free from artifacts on radiogram, CT and MRI images [26]. Several studies have demonstrated its biocompatibility and its mechanical and osteoconductive qualities in vitro [28-32]. Furthermore, compared to PEEK and titanium, silicon nitride has a decreased bacterial activity on its surface [33,34]. Based on good results in vitro, silicon nitride is used in the development of bearings that can improve wear and longevity of knee and hip prosthesis [32].

A preliminary study with silicon nitride interbody cages showed good clinical and radiological results in 2 patients 1 year after a transforaminal lumbar interbody fusion procedure [35]. Sorrell et al. presented the results of a 10 year clinical follow-up study [36]. In this study 30 patients underwent anterior interbody fusion of the lumbar spine using silicon nitride cages. They found a durable interbody fusion after 5 years (21 out of 22 patients) and after 10 years (16 out of 16 patients). Please note there was a 47% loss of follow-up. Silicon nitride materials received the CE Mark and FDA market clearance for its use as interbody cages in 2008. They have been used in the US for over 3 years, with no adverse events reported [32].

Compared to PEEK cages silicon nitride cages are expected to have lower complications rates and allow higher fusion rates due to better biocompatible and osteoconductive qualities. The purpose of this study is to compare the clinical outcomes and fusion rates of PEEK cages with silicon nitride cages in patients with symptomatic degenerative lumbar disc disorders.

## Methods/Design

In our study, PEEK and silicon nitride interbody cages will be compared in the treatment of degenerative lumbar disc disorders. This non-inferiority study is designed as a multi-center (two center) clinical observer and patient blind randomized controlled trial with 2 parallel treatment groups. The multi-center design is needed in order to collect enough patients for reasons of statistical power. To minimize observer bias, both patients and clinical observers will be blinded for treatment during follow-up. Clinical observers will not analyze radiograms and CT because the silicon nitride cages are clearly visible. The follow-up is 2 years, in which patients will fill out several questionnaires and are examined both clinically and radiologically.

### Patient selection

Participation in our study will be requested from patients (18–75 years old) who visit the outpatient clinic in one of the participating hospitals. Patients must present with a history of chronic low back pain with or without leg pain that did not respond to conservative treatment and disc degeneration of Pfirrmann Grade III [37] or higher and/or isthmic or degenerative spondylolisthesis of Grade I or II, confirmed by MRI.

The treating physician will discuss this study with the patient and if the patient fulfills all inclusion criteria (Table 1), the information form and informed consent form is handed out to the patient. The patient can read subsequently at leisure at home.

**Table 1 T1:** Inclusion and exclusion criteria

*Inclusion criteria*	• Male and female patients age 18–75 years
	• Chronic low back pain unresponsive to at least six months of conservative care
	• MRI and standing x-ray evidence of Pfirrmann Grade III or greater disc
	• Degeneration and/or degenerative or isthmic spondylolisthesis of Grade I or II
	• Signed informed consent
*Exclusion criteria*	• Osteoporosis
	• Patients with prior failed fusion at the same level
	• Degenerative scoliosis
	• Degenerative spondylolisthesis greater than Grade II
	• Pregnancy
	• Psychiatric or mental disease
	• Alcoholism (drinking more than 5 units per day)
	• Active infection or prior infection at the surgical site
	• Active cancer
	• Insufficient language skills to complete questionnaires
	• Participation in another study
	• More than two symptomatic levels that need fusion
	• Planned (e)migration abroad in the year after inclusion

Patients who decide to participate in our study are scheduled for an appointment with the researcher at the outpatient clinic of the hospital. During this visit, the patient is extensively informed about the backgrounds, the objectives, the investigational design and the assessments of the investigation and the possible advantages and disadvantages of the investigation. All this information provided by the researcher matches the earlier provided patient information form. The patient is requested to sign the informed consent. Pre-operative baseline data will then be collected for the outcome scores as well as patient’s demography. A neurological examination is performed, the MRI and other tests are reviewed and the surgery is discussed. All patients preoperatively visit an anesthesiologist for standard medical assessment. All patients will be operated under general anesthesia.

### Randomization

Patients who meet the inclusion and exclusion criteria, and have given informed consent are allocated the next available investigational number (Patient ID number) and will be randomly allocated to one of two groups (treatment A or treatment B) by use of a centralized 24-hour computerized randomization system that allows internet randomization (Sealed Envelope Ltd. London). After completing follow-up at 2 years post-surgery both patient and researcher will be informed which cage was used.

### Surgical management

Patients will undergo a transforaminal lumbar interbody fusion with an oblique single PEEK or SiN cage (Amedica Corporation, Salt lake City, Utah) supplemented by pedicle screw fixation, as described by Harms et al. [38]. Design of the PEEK cage is similar to the SiN cage. Autograft bone extracted from locally excised bone from the lumbar spine will be used for cage filling. After surgery, patients will be admitted for 3–4 days. Patients are encouraged to mobilize as soon as possible. A lumbar support orthosis is not prescribed.

### Outcome measurements

Several validated questionnaires described below will be used for outcome assessments. During intake, a basic physical exam with neurological examination (muscle strength, reflexes) and additional assessments as required per normal practice will be performed to ensure that the patient can undergo surgery safely. During follow-up visits at 3, 6, 12 and 24 months the neurological examination will be repeated. See Table 2 for the patient follow-up chart.

**Table 2 T2:** Follow-up chart

	**Intake**	**Admission**	**3 months**	**6 months**	**12 months**	**24 months**
Visit	1	2	3	4	5	6
Demography	X					
Study information + informed consent	X					
Randomization	X					
Surgery		X				
Operative data		X				
Neurological examination	X		X	X	X	X
Questionairres:	X		X	X	X	X
- Roland Morris disability questionairre						
- SF-36						
- VAS back						
- VAS leg						
- Working status						
Likert scale		X	X	X	X	X
X-rays	X	X	X	X	X	X
CT					X	
MRI	X					
Complications		X	X	X	X	X

#### Primary outcome measure

Primary outcome will be measured by the Roland Morris Disability Questionnaire (RMDQ). The 24 point RMDQ is a widely used patient-completed measure of health outcome for low back pain [39-41]. The patient will complete the Dutch version of the questionnaire, which is validated for the Dutch population [42], and the sum of the scores will be used to measure disability. The score ranges from 0 to 24, with a higher score indicating more severe disability. Primary objective is to measure the average improvement in RMDQ for the silicon nitride patients versus those that receive similar-shaped PEEK cages.

#### Secondary outcome measures

*SF-36:* The SF-36 will be used as the generic quality of life questionnaire [43,44]. The SF-36 questionnaire has been applied and validated numerous times for intervention studies with back pain and spine surgery. The questionnaire relates to the analysis of the general functional status of patients. The questions are divided in eight domains:

● Physical functioning

● Physical role limitations

● Emotional role limitations

● Social functioning

● Physical pain

● General mental health

● Vitality

● General health perception

Each domain is converted to a 0 to 100 score, a higher score indicating a better health condition. The eight domains are also combined into a physical and psychological summary score. These are converted to range from 0 to 100 with an average person at 50 and a standard deviation of 10 points.

*Pain (Back and Leg VAS):* The pain intensity in the back and legs are rated by the patient on a 100 mm horizontal visual analog scale (VAS). The two ends of the scale are “no pain” at 0 mm and “the most terrible pain I can imagine” at 100 mm. The patient is asked to mark the scale based on the average pain intensity during the week prior to the visit to the outpatient clinic. During each visit, the patient will complete one VAS for the pain in either leg, and one VAS for back pain.

*Likert score:* Recovery is rated by the patient on a 7-point Likert score in which 1 defines complete recovery and 7 is worse than ever. Likert score will be dichotomized in good recovery (‘complete recovery’ and ‘almost complete recovery’) and bad recovery (‘little recovery’ to ‘worse than ever’). Patient will complete the Likert score at the day of discharge from the hospital and during each follow-up visit.

*Radiographic Images (Plane radiogram, MRI, CT):* A pre-operative MR and a set of standing plane radiograms of the lumbar spine will be collected for all patients. Pre-operative disc degeneration will be evaluated on the MR scan by the method of Pfirrmann [37]. Patient fusion status will be evaluated according to the criteria mentioned by Burkus et al. which are based on qualitative observations [45,46]. Determination of fusion involves the radiographic evaluation of angular changes in spinal alignment, assessment of the device-host interface, and identification of new bone formation and bone remodeling [46]. Anterior – posterior radiograms will be collected after 3, 6, 12 and 24 month. After one year, a CT scan (Siemens sensation 16, 3.0 mm slice) of the lumbar spine will be collected to monitor new bone formation and bone remodeling within and around the central core of the cages. Two radiologists will independently analyze the lumbar radiograms and CT. Disagreement between the radiologists will be resolved by consensus.

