### Statistical considerations

#### Sample size

The sample size calculation is based on the primary objective to compare the silicon nitride and PEEK cages with respect to improvement in RMDQ score and to demonstrate that the silicon nitride cage is non-inferior to the PEEK cage.

In a large spinal fusion cohort study, Robertson [47] found a mean RMDQ improvement of about 10 points. Scheufler also noted an improvement from a pre-treatment score of 17 to 7 at eight months post-op, with a standard deviation of 4 [48]. Both studies included patients with back pain from degenerative disc disease and degenerative spondylolisthesis.

The maximal difference between the treatment arms that could be considered potentially no longer clinically relevant for the RMDQ is thus a difference in improvement of 2–3.5 points [39,41,49]. We therefore consider a non-inferiority margin of 2.6 points between the treatment arms to reflect the maximal difference that is not clinically relevant. Non-inferiority is to be demonstrated based on a one-sided confidence interval with significance level of 2.5% for the difference between the two treatment arms. Assuming a standard deviation of 4 points, 50 patients per arm provide 90% power to demonstrate non-inferiority within a non-inferiority margin of 2.6 points. The total of 100 patients shall be randomized into two groups to minimize bias. This sample size is based on comparing treatment groups with a *t*-test. The actual analysis is a repeated measurements analysis with baseline as covariate, which is more efficient (requiring less patients, at least about 10% if the correlation between baseline and endpoint is 0.3). Thus, no additional sample size increase is incorporated to account for drop-out. Sensitivity analyses to assess impact of drop outs will be performed.

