#### Statistical analysis

The primary analysis will be on the change from baseline in RMDQ score. This will be analyzed based on a mixed model for repeated measurements, including baseline RMDQ as covariate and treatment and center as factors. No imputation will be applied for this analysis. The primary comparison will be at 12 months of follow-up.

Sensitivity analyses to assess impact of drop outs will be performed. These will include an analysis based on Last Observation Carried Forward imputation, as well as multiple imputations based on differential patterns of drop out/missing data reasons.

An exploratory analysis of the distribution of the individual improvements in change from baseline in RMDQ score versus the fusion rate (in three categories) within treatment groups will be performed to assess the extent to which both are consistent.

Other continuous outcomes assessed at each visit will be analyzed similarly. Dichotomous outcomes will be compared between treatment groups based on Z-tests for comparing proportions, with results expressed as 95% confidence intervals for the difference in proportions.

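### The 7-point Likert recovery score is analysed only as good versus bad recovery; adding a full-scale ordinal analysis would be a cheap improvement of low severity

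*Protocol article*

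**What the plan says.** The protocol article, Secondary outcome measures, defines the scale: "Recovery is rated by the patient on a 7-point Likert score in which 1 defines complete recovery and 7 is worse than ever". The next sentence fixes its use: "Likert score will be dichotomized in good recovery" (the two most favourable categories, read here as grades 1 and 2) against everything from little recovery downwards. The score is collected at discharge and at each follow-up visit. Table 2 shows no value at intake.

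The section Statistical analysis does not name the Likert score, but its general rule covers it once it is cut: "Dichotomous outcomes will be compared between treatment groups based on Z-tests for comparing proportions". Each such comparison is to be reported with a 95% interval for the between-arm difference. Continuous outcomes assessed at each visit follow the primary repeated-measures model, which has center as a factor.

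The abstract gives the outcome's rank: "Secondary outcome parameters are the VAS leg, VAS back, SF-36, Likert scale, neurological outcome and radiographic assessment of fusion". The section Sample size concerns the RMDQ alone. No distribution, effect size, margin or power target is given for the Likert score.

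**The concern.** Both the cut and the test are stated, so this concerns a chosen method and not a detail left to an unseen analysis plan. Five of the seven grades become one. A patient with a little recovery counts the same as one who is worse than ever, and complete counts the same as almost complete. The article gives no reason for the cut. The VAS back, VAS leg and SF-36 scores are kept on their full scales. The Z-test also leaves out center, which the model for continuous outcomes includes.

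At stake is how sensitive a supporting comparison is. The Likert score is the only global patient rating of recovery listed, and it is a natural check on the RMDQ result. If one cage moved patients from little recovery to a worse grade, the planned analysis would not register it.

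**Working it through.** **1. The plan's own figure.** Inputs from Sample size: "Assuming a standard deviation of 4 points", margin 2.6, "one-sided confidence interval with significance level of 2.5" per cent, 90% power.

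n per arm = 2 × 4² × (1.960 + 1.282)² / 2.6² = 32 × 10.51 / 6.76 = 49.7, so 50.

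Power at 50 per arm: 2.6 / (4 × √(2/50)) = 2.6 / 0.8 = 3.25, and 3.25 − 1.96 = 1.29, which gives 90.1% (89.6% with the noncentral t). The statement "50 patients per arm provide 90% power to demonstrate non-inferiority within a non-inferiority margin of 2.6 points" is reproduced. It says nothing about the Likert score, so every Likert input below is an assumption.

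**2. Information kept by the cut.** Under proportional odds, with N patients in total, the information on the log odds ratio is about N(1 − Σp³)/12 for the full scale and N·g(1 − g)/4 for the cut. Here p are the grade probabilities and g is the share with good recovery. The ratio is 3g(1 − g)/(1 − Σp³).

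Example with seven equally likely grades: g = 2/7 = 0.286, the numerator is 3 × 0.286 × 0.714 = 0.612, the denominator is 1 − 7/343 = 0.980, and the ratio is 0.625. Over eight assumed distributions with 20 to 70% good recovery, the ratio ran from 0.49 to 0.84 and was above one half in seven of them.

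**3. One case by hand.** Equal grades in the control arm, odds ratio 2, 50 per arm, two-sided 5%.

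- Cut: good recovery goes from 0.286 to 0.444 (odds 0.4 to 0.8), a difference of 0.159. The standard error is 0.0963 under the null and 0.0950 under the alternative. (0.159 − 1.96 × 0.0963)/0.0950 = −0.32, so power is about 38%.
- Full scale: information is about 100 × 0.980/12 = 8.16, and ln 2 × √8.16 = 0.693 × 2.857 = 1.98. 1.98 − 1.96 = 0.02, so power is about 51%.
- Simulation (40,000 runs): 37.7% for the Z-test and 49.6% for the tie-corrected Wilcoxon test, a loss of about 12 points.

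**4. Range under proportional odds.** Simulated power in per cent, Wilcoxon versus pooled Z-test, with the loss in points (differences taken before rounding):

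| Good recovery, control | Information kept | Odds ratio 2 | Odds ratio 3 |
|---|---|---|---|
| 20% | 49% | 49.4 vs 32.6 (16.8) | 87.0 vs 70.5 (16.5) |
| 30% | 65% | 49.3 vs 39.1 (10.2) | 86.4 vs 77.7 (8.8) |
| 40% | 74% | 48.9 vs 42.8 (6.0) | 85.9 vs 78.7 (7.2) |
| 50% | 78% | 48.1 vs 40.4 (7.7) | 85.2 vs 74.3 (10.9) |
| 60% | 77% | 47.1 vs 35.7 (11.4) | 84.1 vs 68.0 (16.1) |
| 70% | 69% | 46.1 vs 30.8 (15.3) | 82.9 vs 58.8 (24.1) |

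Over all eight distributions, the loss was about 1 to 7 points at odds ratio 1.5 and about 4 to 24 points at odds ratios 2 to 4.

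**5. Range under a normal latent shift.** Five assumed distributions with 35 to 80% good recovery in the PEEK arm, 6,000 runs each, Z-test versus Wilcoxon:

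- 0.65 SD: 66 to 74% versus 83 to 87%, a loss of 12 to 21 points.
- 0.5 SD: 45 to 54% versus 63 to 67%, a loss of 12 to 22 points.
- 0.4 SD: 31 to 38% versus 43 to 48%, a loss of 9 to 16 points.
- No shift: 4.5 to 5.8% versus 4.6 to 5.0%.

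The 0.65 SD is 2.6/4, borrowed from the RMDQ. Nothing in the article ties it to the Likert scale.

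**6. Shifts that are not broad.**

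- Worsening only within bad recovery: with 50% good in both arms, and 33% versus 8% of patients in grades 6 and 7, the Z-test rejects in 5.9% of runs (its null rate) and Wilcoxon in 31%. Other assumed examples of this kind gave Wilcoxon 13, 19 and 28%.
- Change only across the cut: with 25 percentage points moved from grade 2 to grade 3, the Z-test has about 74 to 75% power and Wilcoxon about 20 to 23%.

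**The case against.** The best defence is that a prespecified responder proportion, reported with a confidence interval, is a legitimate and readable summary of an unpowered secondary outcome. That stands: the planned analysis is neither an error nor a contradiction. Imprecision would show as a wide interval, and no margin or success rule is attached to the score.

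It also stands that the ordinal test is not uniformly better. Step 6 shows the Z-test well ahead when the effect sits exactly at the cut. It also shows the rank test with only modest power for worsening confined to bad recovery, a pattern that does not fit proportional odds either. The full-scale RMDQ, VAS and SF-36 scores would still be able to show deterioration.

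A reader might infer that the cut takes the score out of a baseline-adjusted model. It does not: Table 2 has no intake value, so there is no baseline to adjust for. The model for continuous outcomes would not necessarily have covered an ordinal item either. Only the center adjustment is absent.

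What the objection does not answer is that the one stated analysis cannot see movement within five of the seven grades, and that it had lower power in every broad-shift scenario with an effect.

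**Conclusion.** The point holds as a low-severity improvement. For broad shifts at 50 per arm and two-sided 5%, the cut keeps about 50 to 85% of the ordinal information and costs about 1 to 24 points of power. The loss is about 9 to 22 points for latent shifts of 0.4 to 0.65 SD. All of this rests on assumed grade distributions and effects.

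Three stronger readings are not supported:

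- That the cut throws away most of the information. The share kept fell just below one half in only one of eight distributions. The power pairs in step 5 agree: the ratio of (z for power + 1.96)² lies between 0.59 and 0.77. For example, 65.7% versus 86.9% gives (0.40 + 1.96)²/(1.12 + 1.96)² = 0.59.
- That any single power loss is a property of this trial. The article contains no Likert inputs from which to derive one.
- That the non-inferiority conclusion is at risk. It is tested on the RMDQ alone and is unaffected.

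**What to change.** In the Likert paragraph and in Statistical analysis, add a prespecified analysis of all seven grades at each follow-up visit. A proportional-odds model with treatment and center as factors would give a common odds ratio with its 95% confidence interval; a Wilcoxon test stratified by center is the simpler option. Keep the good and bad recovery proportions, with the 95% confidence interval of their difference, as the readable summary. Showing the counts in all seven grades by arm would expose movement within bad recovery that neither test detects reliably.

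The cost is wording and one standard model, with no new data, visits or patients. The downsides are one more analysis to report, an effect measure that is less direct than a difference in proportions, and an assumption of roughly proportional odds. The change is best made before unblinding.

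### The only post-operative CT is fixed at 3.0 mm slices, which is coarse for the interface and new-bone criteria of the secondary fusion outcome

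*Protocol article*

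**What the plan says.** Under Secondary outcome measures, the Protocol article fixes the scanner and the slice: "a CT scan (Siemens sensation 16, 3.0 mm slice) of the lumbar spine will be collected to monitor new bone formation and bone remodeling". The purpose given for the scan is "to monitor new bone formation and bone remodeling within and around the central core of the cages". Table 2 marks CT once, at the 12-month visit, and the abstract agrees: "After 1 year the fusion rate will be measured by radiograms and CT". The other sectional examination in the table is the MRI at intake.

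Fusion status follows published criteria "which are based on qualitative observations". They combine change in spinal angle with "assessment of the device-host interface, and identification of new bone formation and bone remodeling". Two radiologists read the radiograms and the CT independently and settle differences by consensus.

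The Background explains why the interface is of interest. It reports that "PEEK cages are generally encapsulated by a thin fibrous tissue layer rather than bone growing in intimate contact with the polymer", and it states the expectation that "silicon nitride cages are expected to have lower complications rates and allow higher fusion rates due to better biocompatible and osteoconductive qualities". Radiographic fusion is a secondary outcome. Under Statistical analysis it also enters, in three categories, an exploratory comparison with individual RMDQ change.

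**The concern.** The article leaves many imaging details open, but it does commit to a slice thickness. That value bears on the direction in which the fusion criteria have to be read. Fusion here means bone running from one vertebra to the next through the cage. The cage's contact surfaces with the endplates, and any gap interrupting the bridge, may lie roughly parallel to axial slices. Resolution across them is then set by slice thickness, and reformats built from 3.0 mm slices would be no sharper in that direction.

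At stake is the quality of one secondary outcome. Fusion is the outcome closest to the material rationale and is part of the purpose stated at the end of the Background. A blurred reading adds misclassification to the comparison between arms and to the fusion-RMDQ analysis, and no later CT is planned against which to check it.

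**Working it through.** **The plan's own figure.** The article gives no calculation for the CT. Its only power statement concerns RMDQ: margin 2.6, SD 4, one-sided 2.5%, 90% power. With n per arm = 2 × SD² × (z₀.₉₇₅ + z₀.₉₀)² / margin², this is 2 × 16 × (1.960 + 1.282)² / 6.76 ≈ 49.8, hence 50 per arm, as stated. The CT does not enter this calculation.

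**Inputs for the CT.** From the article: slice thickness 3.0 mm; one post-operative CT, at 12 months. Assumed, because the article is silent: axial slices, contiguous and 3.0 mm thick as read; disc space 8 to 14 mm; thickness L of a gap or lucent layer 0.1 to 1.0 mm, lying parallel to the slice. The 1.0 mm slice is a comparator chosen for illustration.

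**Slices across the disc space** = height / slice thickness.
- At 3.0 mm: 8/3 = 2.7 to 14/3 = 4.7, so about 3 to 5.
- At 1.0 mm: 8 to 14.

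**Largest share of one slice that the layer can fill** = L / slice thickness, capped at 1.

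| L (assumed) | 3.0 mm slice | 1.0 mm slice |
|---|---|---|
| 0.1 mm | 3% | 10% |
| 0.25 mm | 8% | 25% |
| 0.5 mm | 17% | 50% |
| 1.0 mm | 33% | 100% |

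These are maxima: a layer straddling two slices is divided between them. For any L up to 1 mm, at least two thirds of a 3.0 mm slice is other material. The shares describe averaging within the slice. They are not probabilities of detection.

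**From image to estimate.** If misreading were the same in both arms, the observed difference in fusion proportions would be the true difference × (sensitivity + specificity − 1), that is, shrunk. Equal misreading is not assured. The Methods/Design section says silicon nitride cages are clearly visible on imaging, and the Background calls PEEK radiolucent, so the radiologists can probably tell the cages apart and contrast at the interface may differ by arm. The documents give neither sensitivity nor specificity, so neither the size nor the sign of a bias can be computed.

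**The case against.** A reader might infer that 3.0 mm is too thick to resolve the fibrous layer, so that non-union in the PEEK arm will be read as fusion and the comparison pulled toward no difference. The documents do not support this.

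- **A fibrous layer is not non-union.** The Background reports both encapsulation of PEEK and high fusion rates with PEEK. A patient may have the layer and be fused, so overlooking it does not by itself create a false fusion reading.
- **The layer's thickness is unknown.** At 0.1 mm it would fill only 10% of even a 1.0 mm slice, and thin reconstruction would largely miss it too. Imaging the layer is not an outcome in its own right; the CT's stated task concerns bone in and near the cage core, a larger target.
- **The geometry is not stated.** The article does not say whether 3.0 mm is acquisition or reconstruction thickness, in which plane, or whether reformats are read. Surfaces crossing the slice plane depend on in-plane resolution. A fuller protocol may settle this.
- **CT is not the only evidence.** Angular change and radiograms at 3, 6, 12 and 24 months count as well, and the last of these follow the CT.
- **The formal hypothesis is RMDQ non-inferiority**, which the CT cannot affect.

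All five points stand, and together they remove the stronger reading. They do not remove the narrower one. A failed bridge through the core can itself be a narrow gap across the path of fusion, and the same averaging applies to it. The follow-up films that the section names are frontal views, which show sagittal angle poorly, and the Background itself says a radiolucent cage makes follow-up imaging harder. Two readers in consensus resolve disagreement, but they look at the same images and cannot recover resolution lost in both.

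**Conclusion.** The concern holds in a limited form. A fixed 3.0 mm slice is coarse for two named fusion criteria on the trial's only post-operative sectional examination. Under the assumptions shown (axial contiguous slices, disc space 8 to 14 mm, layer or gap of at most 1 mm parallel to the slice), there are about 3 to 5 slices across the space, and the feature fills at most one third of a slice.

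The likely consequence is some loss of precision in the secondary fusion comparison and in the exploratory fusion-RMDQ analysis. A rate of false fusion readings and a definite direction of bias cannot be derived. The primary RMDQ analysis and its 50 patients per arm are unaffected. This is an inexpensive improvement worth making, not a fault that threatens the trial's main conclusion.

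**What to change.** In Secondary outcome measures, replace the 3.0 mm slice specification with thin reconstruction of the same 12-month acquisition, at about 1 mm or less as far as the acquisition collimation allows. State that both radiologists read sagittal and coronal reformats made from it, and that the settings are identical in both centers. Settle this before the 12-month scans, because raw data may not be kept long enough to reconstruct later. If 3.0 mm is to stay, say whether it is acquisition or reconstruction thickness, name the plane, and justify it against the interface and new-bone criteria.

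The cost is noisier thin images, larger files and slightly longer reading time. No extra scan or reader is needed, and the sample size does not change. The gain is smaller if the collimation does not permit about 1 mm, or if the feature sought is much thinner than that.
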